Meaningful outcomes achieved through intentional sport programming may be mediated by the PYD context, positive relationships, and explicit inclusion of life skills programming within physical activity-centred programming [18, 20–23]. Foundational to positive outcomes of sport programming is the physical and psychological safety of the PYD context [21, 24, 25], necessary for youth to engage fully. Further, relationships between youth and leaders in which leaders are relatable and act as role models, engaging youth to understand and address their individual needs to reach goals with a focus on the future is critical for uptake of programmatic intentions [20, 24, 26]. Leaders can also support development of peer-peer connections to foster a sense of belonging that contributes to both a sense of psychological safety and engagement and retention of youth participants [21]. Programs must have an explicit program theory with an intentional design that is appropriately suited to achieve the desired PYD or SFD outcomes, such as increased life skills and good health behaviours to support academic or occupational achievement [16, 24, 26–28]. Lastly, in sport-based programs, physical activity aimed at promoting the competence, confidence, knowledge, and motivation needed to engage in physical activity for life (termed ‘physical literacy’) [29] and explicit teaching of life skills using sport or physical activity participation as a learning context [20, 26, 27] are most suited for developing PYD assets that may be expected to lead to SFD outcomes.

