We hypothesize that a) volume of participation and b) duration of participation will correlate positively with the primary outcomes listed above.

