#### Core programming

Participants aged 6–12 years will be offered sport plus programs emphasizing physical literacy through a range of activity options. After-school and weekend programs including ball hockey, basketball, multi-sport, soccer, dance, and rock climbing will provide a variety of sports to act as a hook and context for PYD. These programs will have a similar structure and will include dynamic fundamental movements skills, skill and game/performance content specific to the sport, and a cool down and reflection activity. Teaching of life skills will occur through role modelling, discussion, purposefully designed program activities, incentivization and recognition, and the use of teachable moments. Some programs (i.e. multi-sport, ball hockey, football, basketball) will be offered in both co-ed and girls-only formats. The priority of this age group will be the Healthy Body program pillar with the intent to develop physical literacy as PYD asset, allowing for continued engagement in physical activity and sport as youth age out of these programs and setting the stage for additional life skills development.

Participants aged 13–18 years will be offered sport plus programs emphasizing life skills development, including multi-sport, fitness, rock climbing, dance, volleyball, ball hockey, and basketball. Plus sport programs developed in collaboration with local community organizations with demonstrated histories of positive youth impact relevant to the four program pillars will also be offered, including group mentoring programs, a restorative justice program, a kitchen skills-building program, and a social circus program. School day programs for this age group will involve weekly visits by classes from local public schools, and will focus on physical literacy and nutrition education, and exposure to Science, Technology, Engineering and Math topics on-court in a sport setting. All programs will include program-specific sport and life-skill components to achieve the objectives identified for this cohort. Some programs (i.e. basketball, volleyball) will be offered in both co-ed and girls-only programming. The priority for this age group will be the Healthy Mind and Ready for School Pillars, with a secondary emphasis on Healthy Body.

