#### Data analysis

Preliminary analyses will be conducted after 6, 12, and 24 months of recruitment. All statistical analyses will be completed using either SPSS versions 24/25 (IBM) or *R*. Missingness in data will be evaluated for amount of missing data and patterns in missingness. Based on the results of this evaluation, a single mean value imputation method will be applied as needed.

*Ages 6–12:* Repeated measures ANOVAs will be used to examine the main effect of time on physical literacy scores, self-reported physical activity and rates of continued participation in physical activity, controlling for demographic variables such as age and gender. Moderation analyses will be used to explore the effect of program dosage in terms of the number of programs attended over the course of participation in this study on the relationship between time and change in physical literacy. A similar moderation effect will be explored in the relationship between time and the change in self-reported physical activity levels. Pearson’s product-moment correlation coefficients will also be used to explore the relationship between physical literacy and physical activity levels. A standard multiple regression controlling for age, gender, household income and housing status will be used to identify predictive variables for each of the three primary outcomes. Potential predictors for the change in physical literacy include program dosage, type of program involvement (Sport Plus or Plus Sport), physical literacy score at baseline and physical activity level. Potential predictors for the change in physical activity level and rate of continued participation in sport or physical activity include program dosage, type of program involvement, physical activity level at baseline and physical literacy score.

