*Ages 13–18:* Repeated measures ANOVAs will be used to examine the main effect of time on positive health behaviours and each of the six life skills, controlling for demographic variables such as age, gender, household income and race. Moderation analyses will be used to explore the impact of program dosage on the relationship between time and each of the six life skills. Pearson’s product-moment correlation coefficients will also be used to explore the relationship between each of the life skills, positive health behaviors and academic outcomes. Logistic regression will be used to identify predictors of high school graduation for the subset of this age group that would be expected to graduate during the study with possible predictors including scores for each life skill at 2-year follow-up, program dosage and program type, while controlling for gender, household income, housing status and baseline life skills score. The same variables will also be used in a standard multiple regression to identify predictors of continued participation in sport and physical activity in this age group.

*Ages 19–29:* Repeated measures ANOVAs will be used to examine the main effect of time on rate of employment, apprenticeship, or continued training, personal income, and rate of continued participation in physical activity, controlling for demographic variables such as age, education level, household income at baseline and housing status at baseline. Logistic regression will be used to identify predictors of employment status at 2-year follow-up, which may include program type and program dosage (number of programming hours), while controlling for similar demographic variables as identified above for the Repeated Measures ANOVA.

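### Ages 13–18: dose and program type are modelled beside 2-year life skills, so their coefficients for graduation omit whatever the program achieves through those skills

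*Protocol article*

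**What the plan says.** All references are to the protocol article.

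- **Graduation model (Data analysis, Ages 13–18).** A logistic regression is planned whose possible predictors include "scores for each life skill at 2-year follow-up, program dosage and program type, while controlling for gender". The adjustment set goes on to include "household income, housing status and baseline life skills score".
- **Sport model (same paragraph).** "The same variables will also be used in a standard multiple regression to identify predictors of continued participation in sport and physical activity".
- **Pathway.** The Background asks for programs designed to reach outcomes "such as increased life skills and good health behaviours to support academic or occupational achievement". Elsewhere the Background and the Discussion describe life skills as something the programming builds and as what enables young people to engage in school and work.
- **Dose hypothesis.** The secondary hypothesis in Table 1 is that volume and "duration of participation will correlate positively with the primary outcomes listed above". Those outcomes include graduation and continued sport for this cohort. Core programming says volume and duration will serve to examine dose-response on the Table 1 objectives.
- **Other dose analyses.** The Background promises dose moderation for primary outcomes in general. The Ages 13–18 paragraph details it only for the six life skills.
- **Ages 6–12.** Candidate predictors of change in activity and of continued participation "include program dosage, type of program involvement, physical activity level at baseline and physical literacy score". Only the activity term carries a time point.
- **Ages 19–29.** The employment model takes program type and dosage with demographic covariates and no post-baseline score.

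**The concern.** A 2-year life-skill score is measured after the exposure to the program. Because baseline life skills are also adjusted for, the 2-year scores in effect carry the change in skills during participation, which the program sets out to produce. The same paragraph treats these skills as an outcome of dose in the moderation analyses and then as covariates beside dose in the regressions.

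A coefficient for dose or program type with those scores held fixed answers a narrower question: does dose relate to graduation among youth who end with the same life skills? The Table 1 hypothesis asks whether dose relates to graduation at all. The Background says the regressions are meant to inform programming. A weak, null or negative dose coefficient could therefore be taken to mean that more participation does not help, when it only shows that the part working through life skills has been removed.

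**Working it through.** **1. No figure to reproduce.** The Sample size section gives power for large effects on other variables (99.5–100% at n = 100 for ages 13–18). It gives none for these regressions, and no effect size for dose on skills or skills on outcome. Everything numerical below is an assumption used to show direction and range.

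**2. The algebra.** Let each of the six 2-year skills rise by *a* per SD of dose, let the outcome rise by *b* per unit of each skill, and let *c* be the dose effect by all other routes.

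- Overall dose effect = *c* + 6*ab*.
- Dose effect with error-free 2-year skills held fixed and no unmeasured common cause = *c*.

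With *a* = 0.3 and *b* = 0.2, the part through life skills is 6 × 0.3 × 0.2 = 0.36. If *c* = 0, the coefficient goes from 0.36 to 0. If *c* = 0.36, it goes from 0.72 to 0.36.

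**3. Unmeasured common cause.** Suppose an unmeasured standard normal factor U enters each skill and the outcome with weight *u* = 0.4, and the skill residual SD is 0.7 (variance 0.49). Given skills, baseline and dose, the expected U falls per SD of dose by

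(*u*/0.49) × 6*a* / (1 + 6*u*²/0.49) = 0.8163 × 1.8 / 2.9592 = 0.497.

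The bias in the linear dose coefficient is −0.4 × 0.497 = −0.20, so with *c* = 0 the coefficient is −0.20 although dose helps.

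**4. Simulation.** 2-year skill = 0.5 × baseline + *a* × dose + *u* × U + 0.7 × noise. The outcome depends on the sum of the six skills (weight *b*), plus *c* × dose and *u* × U. The models contain dose and six baseline skills, without and then with the six 2-year skills. Imperfect reliability adds error to both baseline and 2-year scores. There were 60 runs at n = 5000 and 400 at n = 100; tests are two-sided at 5%.

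Dose coefficient at n = 5000, without → with 2-year skills:

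| Scenario | Linear | Logistic |
|---|---|---|
| Full mediation, no error | 0.36 → 0.00 | 0.35 → 0.00 |
| Full mediation, reliability 0.8 | 0.36 → 0.10 | 0.36 → 0.10 |
| Full mediation, reliability 0.7 | 0.36 → 0.14 | 0.36 → 0.15 |
| Full mediation, common cause U | 0.36 → −0.20 | 0.30 → −0.20 |
| Half by other routes (*c* = 0.36) | 0.72 → 0.36 | 0.71 → 0.37 |

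Rejection rate for dose at n = 100, without → with:

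| Scenario | Linear | Logistic |
|---|---|---|
| Full mediation, no error | 0.89 → 0.03 | 0.40 → 0.06 |
| Full mediation, reliability 0.8 | 0.91 → 0.10 | 0.45 → 0.09 |
| Full mediation, reliability 0.7 | 0.91 → 0.17 | 0.40 → 0.09 |
| Full mediation, common cause U | 0.67 → 0.36 | 0.33 → 0.14 |
| Half by other routes | 1.00 → 0.63 | 0.89 → 0.20 |

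In the common-cause row the average coefficient with 2-year skills is negative, so the rejections that remain point mainly the wrong way.

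**5. Limits.** The graduation model applies only to those expected to graduate during the study, a subset of unstated size. The n = 100 rates illustrate the loss and are not the trial's power. No simulation was run for program type; the reasoning in step 2 carries over, but no size is attached.

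**The case against.** A reader might infer that a program working exactly as its theory says must show a dose effect of zero. The documents do not support that. Zero needs life skills to carry the whole effect and to be measured without error. The Background names health behaviours beside life skills, Wrap-around services offers direct help through a homework club, and the scales are short self-reports. The Theory of Change figure is not available to settle the pathways.

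A reader might also infer that life skills are the stated route to continued sport. The text ties them clearly to school and work. For lasting activity, the stated route is physical literacy (Core programming, for ages 6–12: "with the intent to develop physical literacy as PYD asset, allowing for continued engagement in physical activity and sport"). The concern is firm for graduation and conditional for sport.

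Nor can the 6–12 model be said to share the fault. Its physical literacy score has no time point and may be the baseline one. Dose on change in physical activity also has its own moderation analysis there. Only continued participation is left open.

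Finally, the terms are possible predictors in an exploratory search, and the dose hypothesis is not formally assigned to these regressions. That is fair and lowers the severity. Joint entry is still the natural reading, and no dose model without the 2-year scores is detailed for either outcome. The 2-year time point is stated outright, so this is not simply detail left to a fuller plan.

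**Conclusion.** The point holds for the 13–18 graduation model. On joint entry, the dose and program-type coefficients exclude whatever acts through life skills and so do not estimate the overall relation the protocol hypothesises. For a program that works, they can be attenuated, near zero or of the wrong sign. Which of these occurs depends on the share mediated, scale reliability and unmeasured common causes, none of which the documents quantify. For continued sport it holds to the extent that life skills affect participation. For ages 6–12 it is a matter of fixing a time point.

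This should be fixed but is not critical. The regressions are exploratory and the repeated-measures analyses are untouched. Dose is self-selected (Study design), so even a corrected coefficient is an observational association.

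**What to change.** - **Ages 13–18.** Judge dose and program type for graduation and continued sport from a model with baseline covariates only, baseline life skills included. The 19–29 employment model already leaves out post-baseline scores.
- **2-year life skills.** Report the model that contains them separately, labelled as a prediction or mediation analysis. State that the overall dose or type effect is not to be read from it.
- **Ages 6–12.** Specify the baseline physical literacy score in the model that judges dose for continued participation.

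The cost is a change of wording and one additional model per outcome, on data already planned. The dose estimate stays open to confounding by self-selection and should be reported as such.

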i. Physical activity minutes/day ii. Health Behaviours iii. Continued engagement in sport	One-week pedometry producing at least 3 days of valid data with a minimum wear time of 10 h/day Healthy Behaviour Questionnaire 6-item, author-designed scale used to measure behaviours relating to sleep, nutrition, physical activity, smoking, substance use, and risky sexual behaviour Self-report of regular sport/physical activity participation
Participants aged 18–29	
a) Employment	Indicator:
i. Employment Status ii. Personal Income	Self-report of placement in job, apprenticeship or training; full- or part-time Self-report of personal income level
b) Sport Participation	Indicator:
i. Continued engagement in sport	Self-report of regular sport/physical activity participation

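### Outcomes that read as categorical are assigned to repeated measures ANOVA (placement, sport participation) or linear regression (sport participation only), and the graduation model uses life-skill scores taken at or after graduation

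*Protocol article*

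**What the plan says.** **Outcomes.** Table 3 of the protocol article gives the employment indicator at the oldest ages as "Self-report of placement in job, apprenticeship or training; full- or part-time" and the income indicator as "Self-report of personal income level". In all three age groups the sport indicator is "Self-report of regular sport/physical activity participation". No response format is given for the sport or income items.

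**Change over time (Data analysis).** At ages 19–29: "Repeated measures ANOVAs will be used to examine the main effect of time on rate of employment, apprenticeship, or continued training, personal income", followed by the rate of continued participation, adjusted for demographic variables. At ages 6–12 the same method examines the "main effect of time on physical literacy scores, self-reported physical activity and rates of continued participation in physical activity", adjusted for variables such as age and gender.

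**Predictors (Data analysis).** At ages 6–12 a standard multiple regression "will be used to identify predictive variables for each of the three primary outcomes", one of which is continued participation. At ages 13–18 the plan uses a "standard multiple regression to identify predictors of continued participation in sport and physical activity in this age group". Employment status at 2 years (ages 19–29) and high school graduation (ages 13–18) are given logistic regression.

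**Graduation model.** It is fitted to the 13–18-year-olds due to graduate during the study, with "possible predictors including scores for each life skill at 2-year follow-up, program dosage and program type". It controls for gender, household income, housing status and baseline life skills score.

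**The concern.** Repeated measures ANOVA and ordinary multiple regression model a mean with constant residual variance. Placement is a category, and regular participation most likely is one too. The section already chooses logistic regression for two binary outcomes, so its choice of linear regression for continued participation is hard to explain.

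This reaches outcomes that matter. Employment status is the variable on which the Sample size section powers the 19–29 cohort, and Table 1 lists continued participation as a primary hypothesis in every cohort.

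The second fault concerns timing. The last assessment is at 24 months. A life-skill score from that visit cannot forecast a graduation that has already happened, and graduating may itself change self-esteem or grit.

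**Working it through.** The plan gives no figure for this point that can be recomputed. The 100% power for employment status comes without rates, and nothing below changes a sample size.

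**1. Which outcome gets which model**

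- Placement, 19–29: ANOVA for time; logistic regression for predictors.
- Continued participation, 19–29: ANOVA for time.
- Continued participation, 6–12: ANOVA for time; linear regression for predictors.
- Continued participation, 13–18: linear regression for predictors.
- Income level, 19–29: ANOVA for time.

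**2. The time test on a 0/1 outcome**

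With n participants, k visits and no covariates, the ANOVA F statistic is a function of Cochran's Q: F = (n−1)Q / [n(k−1) − Q]. The two tests should therefore nearly agree. Simulation under no change used four visits, prevalence 10%, 30% or 50%, latent correlation either 0.5 throughout or 0.4 to the power of years apart, and 4,000 data sets per setting:

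- n = 150: type I error 4.8–5.4% (ANOVA) against 4.7–5.3% (Cochran's Q).
- n = 60: 4.2–5.6% against 4.1–5.5%.

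For assumed rises from 30% to 60% or from 5% to 70% at n = 150, power is about 100% with either. Covariate adjustment was not simulated.

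**3. What the time model gets wrong**

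- The variance of a 0/1 outcome is p(1−p): 0.25 at 50% and 0.09 at 90%, a ratio of 2.8. Adjusted effects are forced to be additive on the probability scale with one common variance.
- Full- or part-time placement must either be collapsed, losing the distinction, or scored. A 0/1/2 score equates the step from none to part-time with the step from part-time to full-time. Job, apprenticeship and training have no natural order.

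**4. Linear regression on a yes/no outcome**

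Counting each listed variable as one term, the 6–12 model has 8: age, gender, household income, housing status, dosage, program type, baseline activity and physical literacy. The 13–18 participation model reuses the graduation list. That is 6 two-year scores + dosage + program type + 3 demographic variables + 1 baseline score = 12, or 17 if all six baseline scores enter.

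With no true effect, fitted values scatter around prevalence p with SD ≈ √[p(1−p)·k/(n−1)], where k is now the number of predictors:

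- p = 0.9, n = 150, k = 8: √(0.09 × 8/149) = 0.070; (1 − 0.9)/0.070 = 1.44; about 7.5% exceed 1.
- p = 0.9, n = 100, k = 17: √(0.09 × 17/99) = 0.124; 0.1/0.124 = 0.80; about 21% exceed 1.

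Simulated shares outside 0–1, from no effect to moderate effects (log-odds slopes up to 1 per SD, or total log-odds SD up to 1):

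| Prevalence (assumed) | n = 150, 8 predictors | n = 100, 17 predictors |
|---|---|---|
| 50% | 0–7% | 2–11% |
| 70% | 0.5–7% | 6–12% |
| 90% | 7–21% | 21–26% |

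With one predictor, n = 100, slopes of 1–2 and prevalence 50–90%, the share is 2–17%. Much of the largest figure is overfitting, since 21% arises with no effect at all.

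**5. Timing of the graduation predictors**

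Follow-up ends at 24 months, so a graduation within it comes before or at that visit. Assuming end-of-June graduation, four example baselines (late February, June and September 2017, and late March 2018) put the 2-year score about 3 to 24 months after graduation. With a baseline at the start of July the two can nearly coincide.

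**6. Size of the graduation model**

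The Recruitment section gives February 2017 to September 2019 (11 + 12 + 9 = 32 months), with data collection ending on 31 March 2020. A 24-month visit needs a baseline by 31 March 2018, which is 14 months: 14/32 = 43.75%, or about 44 of 100 youths if accrual is even. If a third to a half are due to graduate (assumed), 14–22 remain. With 20% not graduating (assumed), the smaller outcome group is 3–4. At the most favourable split, half and half, it is 7–11, still below one per term for 12 terms. If all 100 reached 24 months, 33–50 would be in the subset, with 7–10 not graduating at 20%.

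**The case against.** The strongest reply is that the headline test works. A reader might infer that the ANOVA time test on a yes/no outcome is invalid; step 2 does not support that for the unadjusted test. A reader might also infer that employment goes through linear regression. It does not: its predictor model is logistic. Using one model for change over time and another for prediction at a single visit is not in itself a contradiction.

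The response formats of the sport and income items are inferred, and a condensed article may leave item coding to the full protocol. The word rate fits a yes/no item but does not prove it. The out-of-range shares depend on a prevalence that no document gives.

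On graduation, the text offers possible predictors, not a fixed model; the baseline score is written in the singular, so 17 terms is speculative; and the regressions are meant to inform programming. All of this stands.

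It does not remove the point. Placement is categorical on the face of Table 3, the model choices are stated outright, and the list offers no life-skill score from a follow-up visit before graduation in place of the 2-year ones.

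**Conclusion.** The point holds in a limited form. The stated models do not suit placement, or continued participation if that item is yes/no as it reads. The harm lies in adjusted effects, category scoring and linear regressions with near 0% to about 25% of fitted probabilities out of range. It does not lie in the type I error of the unadjusted time test. The fault in adjusted effects rests on reasoning, not simulation.

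The 2-year scores in the graduation model cannot be read as predictors of a graduation within follow-up. A reader might go further and say that the model reverses cause and effect or cannot be estimated. The first is not shown: late measurement makes the direction unreadable, which is a weaker claim. The second needs even accrual, an assumed share due to graduate, an assumed share not graduating, and entry of every listed term. What the calendar supports is that 12 or more terms are probably too many.

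**What to change.** - **Placement and continued participation over time:** use GEE or mixed logistic models with visit as a factor, and report the change in proportion with its confidence interval. Use an ordinal model where the categories are ordered, including income if it is collected in bands.
- **Predictors of continued participation, ages 6–12 and 13–18:** replace standard multiple regression with logistic regression if the item is yes/no. State the response format.
- **Graduation:** admit only life-skill scores measured before graduation (baseline or the last prior visit), and limit the number of predictors to what the observed number of events supports. How to shorten the list is the investigators' choice.

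The cost is wording only. No visit, measurement or sample size changes; the graduation model becomes smaller.
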